## Abstract

**Background:**

Women with breast cancer undergoing chemotherapy suffer from a range of detrimental disease and treatment related side-effects. Exercise has shown to be able to counter some of these side-effects and improve physical function as well as quality of life. The primary aim of the study is to investigate and compare the effects of two different exercise regimens on the primary outcome cancer-related fatigue and the secondary outcomes muscle strength, function and structure, cardiovascular fitness, systemic inflammation, skeletal muscle gene activity, health related quality of life, pain, disease and treatment-related symptoms in women with breast cancer receiving chemotherapy. The second aim is to examine if any effects are sustained 1, 2, and 5 years following the completion of the intervention and to monitor return to work, recurrence and survival. The third aim of the study is to examine the effect of attendance and adherence rates on the effects of the exercise programme.

**Methods:**

This study is a randomised controlled trial including 240 women with breast cancer receiving chemotherapy in Stockholm, Sweden. The participants are randomly allocated to either: group 1: Aerobic training, group 2: Combined resistance and aerobic training, or group 3: usual care (control group). During the 5-year follow-up period, participants in the exercise groups will receive a physical activity prescription. Measurements for endpoints will take place at baseline, after 16 weeks (end of intervention) as well as after 1, 2 and 5 years.

**Discussion:**

This randomised controlled trial will generate substantial information regarding the effects of different types of exercise on the health of patients with breast cancer undergoing chemotherapy. We expect that dissemination of the knowledge gained from this study will contribute to developing effective long term strategies to improve the physical and psychosocial health of breast cancer survivors.

**Trial registration:**

OptiTrain - Optimal Training Women with Breast Cancer (OptiTrain), NCT02522260; Registration: June 9, 2015, Last updated version Feb 29, 2016. Retrospectively registered.

## Background

It is well established that exercise has the potential to improve the health of cancer survivors; [1] however, evidence is still lacking on the benefits of different modalities of exercise and different exercise prescriptions on many common disease and treatment-related side-effects. Even less is known about the specific effects of different types of exercise on the most commonly reported side-effect, cancer-related fatigue [2–4]. Additionally, many existing exercise studies have been short in duration and lack follow-up assessments; thus, the long term-effects and sustainability of the exercise programme are not monitored or assessed. The few large randomised controlled exercise interventions in patients with breast cancer during chemotherapy have shown improvements in physical function, fatigue, and health-related quality of life (QoL) compared to patients receiving standard care [5, 6]. Differences have also been identified when comparing moderate or vigorous to a low intensity exercise program, demonstrating greater beneficial effects on QoL and physical function with moderate or vigorous exercise [7]. To develop exercise interventions and guidelines that have the potential to address the great problems facing cancer survivors, adequately-powered trials with long term follow-up are urgently required.

After a cancer diagnosis and during treatment, a marked deterioration of the individual’s physical capacity usually ensues and it is well known that patients with cancer generally reduce their activity levels after diagnosis [8]. Many patients are also forced to adapt their daily activities [9, 10] and side-effect symptoms resulting from treatment for cancer greatly affect the patients’ QoL. Previous research shows that QoL is a prognostic factor for patients with breast cancer that correlates with both survival and how well patients respond to treatment [11]. Although medications that target estrogen receptors decrease the risk for recurrence by approximately 50%, aromatase inhibitors result in detrimental musculoskeletal side-effects [12], possibly due to the influence of muscle protein turnover [13]. Other side-effects that patients with breast cancer encounter include cardiovascular complications, psychological distress [14] and increased levels of pain [15].

Despite growing research in oncology and physical exercise there is a paucity of randomised controlled trials that have particularly focused on investigating which modalities of exercise are most beneficial and at which intensity, duration and frequency these exercise modalities should be prescribed to reduce the side-effects and improve the health of patients with breast cancer [16]. While exercise trials for patients with cancer have generally employed either resistance or aerobic exercise, there is a lack of studies that have combined the two training modalities [1].

Significant barriers exist for patients with cancer who wish to return to work [17]. Exercise provides a potential strategy to improve the physical and mental health of survivors, in turn improving their likelihood to return to work, should they chose to. The PACES randomised clinical trial demonstrated that patients who were prescribed moderate to high intensity combined aerobic and resistance exercise or were prescribed light intensity physical activity during chemotherapy returned to work significantly earlier and for longer hours than the standard care group at the end of a 6-month intervention period [18]. As survival rates for breast cancer increase, facilitating successful return to work rates is of great importance.

Attendance and adherence to exercise protocols have generally been poorly monitored and reported in the existing literature, which may have resulted in an over- or underestimation of the effects of exercise programs. Investigation of the importance of adhering to exercise protocols and rates of attendance is warranted to understand the real- world implications of these exercise programs.

The molecular mechanisms induced by exercise in patients with cancer are still largely unknown. Low-grade systemic inflammation is linked to most events involved in the development and progression of cancer [19] and an ongoing elevated systemic inflammatory state is associated with poor prognosis in patients with cancer [20]. Findings on anti-inflammatory effects of physical exercise have mainly been demonstrated in healthy individuals showing that regular exercise exerts anti-inflammatory effects [21, 22]. Few studies have evaluated the effects of exercise on inflammatory markers after a cancer diagnosis and data on inflammatory responses to exercise during chemotherapy are even scarcer but tend to show exercise-induced anti-inflammatory effects [23, 24]. Those data are, however, confounded by heterogeneous patient populations, small sample sizes, and analysis of only a few pro/anti-inflammatory biomarkers [25]. Moreover, the effect of different types and doses of standardised exercise on inflammatory markers in patients with cancer need to be elucidated.

The current study will examine and compare the effects of different modalities and intensities of exercise on a wide range of clinically important and varying endpoints in patients with breast cancer. It will be the first study of its kind to offer supervised exercise sessions in the clinical setting that includes strategies to monitor physical activity levels over the course of and after the 16-week supervised intervention period including multiple follow up measurements (1, 2, and 5 years). In addition to functional outcomes, important biomarkers of systemic inflammation and skeletal muscle gene activity will be assessed. This can translate into better take out well-informed and targeted strategies for surveillance and treatment of patients with breast cancer.

The primary aim of the study is to compare the effects of two different exercise regimens (aerobic exercise vs. a combination of aerobic and resistance exercise) and a usual care control group on the primary outcome cancer related fatigue and the secondary outcomes cardiovascular fitness, muscle strength, function and structure, systemic inflammation, gene activity, health related quality of life, pain, disease and treatment related symptoms in patients with breast cancer receiving chemotherapy. The second aim is to examine if these effects, if any, are sustained one, two, and five years following the completion of the intervention and to monitor the effects of the intervention on return to work, recurrence and survival. The third aim of the study is to examine the effect of attendance and adherence rates on the effects of the exercise programme.

## Methods/design

### Study design

This study is a 16-week randomised controlled exercise trial with follow-up at one, two and five years. The modified SPIRIT study flow chart is shown in Fig. 1. Briefly, the participants are randomly allocated to either: group 1: Aerobic exercise training (AT) twice a week for 16 weeks, group 2: Combined resistance and aerobic exercise training (CT) twice a week for 16 weeks, or group 3: usual care (UC) (control group) with physical activity information but no supervised training. To support the women to maintain exercising after the intervention during the 5-year follow-up period, participants in the exercise groups will receive a physical activity prescription, access to public gyms and invitations to regular motivational information seminars.

**Fig. 1 Fig1:**
[figure not shown]
The modified SPIRIT study flow chart

### Study setting

The study centre, testing and exercise clinic are located at Karolinska University Hospital, and Karolinska Institutet, Stockholm, Sweden.

### Ethics

Ethical permissions (with numbers 2012/1347-31/1, 2013/632-32 and 2014/408-32) have been obtained from the Regional Ethical Review Board in Stockholm. All participants will provide informed written consent prior to their entry into the study. In the case that changes in the protocol are necessary, relevant amendments will be made and submitted to the relevant ethics trial registration authorities.

### Participant recruitment

Recruitment began in March 2013 and is ongoing. Two-hundred and forty (80 in each group) women with breast cancer undergoing chemotherapy are being recruited from the Department of Oncology Breast and Sarcoma units at Radiumhemmet and Södersjukhuset, Karolinska University Hospital in Stockholm, Sweden. The expected completion date for recruitment is August 2016. Oncology physicians inform eligible patients about the study and, should they wish to participate, they fill in a cardiovascular health questionnaire and undergo an echocardiogram. If no relevant cardiovascular health issues are identified, the participants are deemed fully eligible for the trial. Once the participants have had any of their possible questions answered to their satisfaction and wish to volunteer for the study, the participants then sign the written informed consent form prior to data collection. Research nurses at The Clinical Trials Unit at Radiumhemmet then inform the study researchers of the participant’s eligibility and of the group allocation of the patient.

### Eligibility criteria

Inclusion criteria include women (aged 18–70 years) with Stage I-IIIa breast cancer about to start adjuvant chemotherapy. Exclusion criteria are assessed by study researchers and include patients with advanced disease, patients where physical activity is contraindicated because of safety reasons such as uncontrolled cardiovascular disease, brain or bone metastases, cognitive dysfunction, and patients who do not speak or understand the Swedish language.

### Randomisation process

The participants are randomly allocated by the Clinical Studies Unit at Radiumhemmet, Karolinska University Hospital (Stockholm, Sweden) to either AT, CT, or UC at a 1:1:1 ratio using a computer-generated program. A randomly selected subset of participants (*n* = 45) will also undergo a muscle biopsy before and after the intervention.

### Blinding

As this is an exercise intervention, participants cannot be blinded to group assignment. Outcome assessors are not blinded to group allocation, with the exception of assessors of muscle biopsy and blood samples who are blinded to group allocation.

### Testing

Data collection will occur prior to, directly after and at one, two and five years following the completion of the 16-week intervention period as shown in Fig. 1. The primary outcome is fatigue. Secondary outcomes are return to work, muscle strength and function, cardiovascular fitness, systemic inflammation, mitochondrial density, muscle fibre area, QoL, pain, disease status and treatment-related symptoms.

### Primary outcome

The Piper Fatigue Scale is being used to subjectively assess fatigue in four dimensions: behavioral/severity, affective meaning, sensory, and cognitive/mood [26]. The scale has been shown to have psychometric properties that are reliable for assessing subjective dimensions of fatigue among Swedish populations of patients with cancer [27].

### Secondary outcomes

Muscle strength is being assessed by a hydraulic hand dynamometer (JAMAR, SAEHAN corporation, Changwon, S. Korea), and isometric mid-thigh pull (Baseline leg dynamometer, Fabrication Enterprises Inc., White Plains, NY, USA) and cardiovascular fitness (predicted maximal oxygen uptake, VO_2max_) is being assessed by a sub-maximal exercise test on a cycle ergometer (Monark 928E, Monark Exercise AB, Vansbro, Sweden). Pressure pain thresholds are assessed using a pressure algometer (Somedic Sales AB, Hörby, Sweden). Blood sampling and muscle biopsy procedures are taking place at the Clinical Trial Unit laboratory at Radiumhemmet, Karolinska University Hospital, Stockholm. Muscle biopsies (approximately 100 mg) will be obtained under local anesthesia from the vastus lateralis muscle (lateral part of the knee extensor muscle) with a Bergström needle [28]. This takes place before the intervention starts and 24–72 h after the last training session. Contractile function, markers for systemic inflammation, muscle fiber area, mitochondrial density, and expression of genes important for muscle adaptation will be analysed. Concurrently, venous blood is sampled for markers of systemic inflammation, hemoglobin levels, genotyping, and for analysis of white cell distribution and epigenetic patterns.

Patient-reported outcomes include self-reported health-related QoL assessed by the European Organization for Research and Treatment of Cancer (EORTC QLQ-C30) questionnaire which is a cancer-specific instrument that measures health-related QoL in terms of physical, emotional, social, cognitive and everyday function. Common cancer-related symptoms are assessed by the Memorial Symptom Assessment Scale (MSAS) [29]. The instrument has been validated for Swedish patients with breast cancer [30].

### Additional measures

Additional measures include height, body mass, exercise session attendance and adherence, haematological parameters, cancer treatment, recurrence, survival data, sick leave data, co-morbidities, and cause of death in relevant registers. Sense of coherence (SOC) will also be assessed by a questionnaire (SOC short version which consists of 13 questions) that all participants complete once at baseline testing [31]. The Swedish version of the SOC-13 has been shown to have good validity and reliability. It has also demonstrated high internal consistency [32]. Participants are being asked to wear an accelerometer (ActiGraph model GT3X+, ActiGraph LCC, Pensacola, FL, USA) on an elastic belt over the right hip during all waking hours, except during water based activities for seven consecutive days directly after baseline testing, at one, two and five years after the initial 16-week intervention to objectively record daily activity (sedentary behaviour and physical activity) patterns. Data will be analysed using standardised cutoff points and valid wear-time criteria [33]. Participants will also be asked to complete an Activity Diary to assess daily subjective physical activity during the 16-week intervention period.

### Data entry, management and analysis

Data is collected and entered exclusively by the study research staff. All hard copies of forms are kept in a locked filing cabinet at Karolinska Institutet. Data are entered into computer files in a re-identifiable format (participant numbers only) and password protected. Participants will not be identified in the resulting manuscripts and reports. The data monitoring committee for the current study is made up of the research project staff only and does not include representatives from the funding bodies, nor will it be influenced in any way by these funding bodies. Only the study researchers have access to the dataset.

### Confidentiality

Information collected directly from participants will be in re-identifiable form and any information collected for, used in or generated by this project will not be used for any other purpose. Only the study investigators will have access to study information.

## Intervention

### Phase I: Initial intervention- Supervised exercise training

Participants in the exercise groups begin training the week after the initial testing session which takes place prior to the patients’ second session of chemotherapy. Both exercise groups train twice per week on non-consecutive week days for 16 weeks. Each session is approximately 60 min in duration and is conducted at the exercise clinic at the Karolinska University Hospital. An exercise physiologist or oncology nurse supervises all sessions to ensure safety, correct technique and adherence to the exercise protocols. Participants can choose to perform the continuous aerobic exercise on a cycle ergometer, elliptical ergometer, or treadmill, the interval aerobic exercise is performed on a cycle ergometer. Resistance exercises are performed using machine resistance training equipment, participants’ body weight and free weight dumbbells and barbells. All exercise sessions commence with a five min warm up on a cycle ergometer, treadmill, or rowing machine at a rating of perceived exertion (RPE) of 10–12 on the Borg scale [34] and sessions conclude with a 10 min cool-down which includes dynamic and static muscle stretching activities of the major muscle groups.

Group 1 (AT) exercise sessions commence with 20 min of moderate intensity continuous aerobic exercise at an RPE of 13–15. This is followed by 3 × 3 min bouts of high intensity intermittent aerobic exercise at an RPE of 16–18 interspersed with ~1 min of passive or active recovery.

Group 2 (CT) completes both resistance exercises and high intensity intermittent aerobic exercise during each session. The resistance training regimen consists of 8 exercises (leg press, biceps curls, triceps extensions, bench press, shoulder press, standing row, sit ups/Russian weighted abdominal twist, and prone lying back extensions. Participants complete 2 sets of 8–12 repetitions at an initial intensity of 70% of their estimated 1 repetition maximum (1-RM) strength, and increase to 80% of estimated 1-RM when more than 12 repetitions can be correctly performed by the participant. Every four weeks estimated 1-RM strength tests are performed to ensure progression. Group 2 also completes 3 × 3 min bouts of high intensity intermittent aerobic exercise (RPE = 16–18) interspersed with ~1 min of passive or active recovery.

Group 3 (UC) serves as the control group and receive usual care for breast cancer and general information on physical activity but no supervised exercise training or prescription.

### Phase II: Follow up - Support to maintain physical activity after the intervention

Physical activity on prescription (PAP) is a personalised written prescription of physical activity [35] that will be used to support the women participating in the two exercise arms to maintain their physical activity levels throughout the entire duration of phase II of the study. Participants will have the opportunity to train at the gymnasium operator Friskis & Svettis at locations throughout Stockholm. Motivational seminars on a healthy lifestyle, fitness, and training options will be held in collaboration with Friskis & Svettis three times a year at their facility in Hagastaden, Stockholm. The research team will be responsible for providing the motivational seminars and physical activity prescriptions.

## Statistical analyses

Data will be analysed using the IBM SPSS (Statistical Package for the Social Sciences) 20 statistical package for Windows (SPSS, Chicago, IL, USA). Analyses will include standard descriptive statistics (one-way ANOVAs or Kruskall-Wallis tests, as appropriate, and Chi squared tests). ANCOVAs accounting for baseline values will be used for the main analysis. Variables with data that are not normally-distributed will be log transformed prior to ANCOVA analyses. Paired t-tests or Wilcoxon signed rank tests, as appropriate, will be used to test for within groups differences from baseline to follow up. All tests will be 2-tailed and statistical significance set at *p* ≤ 0.05. An intention-to-treat approach will be used for the analyses with missing values replaced using the expectation-maximization method.

Power Calculation: With fatigue as the primary outcome measure, a sample size of 65 patients/group is required, based on an effect size of 0.53 and power = 0.8. From our research group’s experience with participant dropout in previous exercise trials in cancer survivors, we accounted for an attrition rate of ~20% and therefore are aiming to recruit 80 participants into each group.

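### The rule to log-transform any non-normal variable also covers the primary fatigue score, so the trial's own data decide whether the main result is a mean difference or a ratio

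*Protocol article*

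**What the plan says.** The protocol article, under Statistical analyses, names the main analysis: "ANCOVAs accounting for baseline values will be used for the main analysis". The next sentence sets the transformation rule: "Variables with data that are not normally-distributed will be log transformed prior to ANCOVA analyses". It is worded as a commitment and exempts no outcome.

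The rule therefore reaches the primary outcome (Primary outcome section: "The Piper Fatigue Scale is being used to subjectively assess fatigue in four dimensions"). It also reaches the patient-reported secondary outcomes, namely the "European Organization for Research and Treatment of Cancer (EORTC QLQ-C30) questionnaire" and the Memorial Symptom Assessment Scale (MSAS).

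Non-parametric alternatives appear only elsewhere. Kruskal-Wallis is listed among the descriptive statistics, and for change within a group the article says: "Paired t-tests or Wilcoxon signed rank tests, as appropriate, will be used to test for within groups differences". None is named for the between-group ANCOVA. The article states no score range for any of the three questionnaires.

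**The concern.** Four features make this a poor rule for questionnaire scores.

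- **Wrong object.** ANCOVA assumes roughly normal residuals, not a normal raw variable. With 65 to 80 women per arm, a comparison of means tolerates moderate departures anyway.
- **Direction ignored.** A log pulls in a long right tail. If scores cluster at the high end, it stretches the left tail and increases the skew.
- **Effect measure left to the data.** On the raw scale ANCOVA estimates a difference in means. On the log scale it estimates a ratio of geometric means. Which of these is the primary result is settled only after the distribution has been seen.
- **Zeros.** log(0) does not exist. If zero is a possible score, something must be done with those women, and the answer depends on what is done.

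The main thing at stake is a primary effect whose scale is not fixed in advance and is hard to interpret. A loss of power is a second, conditional risk.

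**Working it through.** **The plan's own figure.** The only figure in the section is the sample size: 65 per group for effect size 0.53 and power 0.8. The two-group formula gives n = 2(1.960 + 0.842)²/0.53² = 55.9, so 56 (57 with the t distribution). Dividing by 0.864, the minimum efficiency of a rank test, gives 55.9/0.864 = 64.7, which matches 65, although the article names no such test. For attrition, 65/0.8 = 81.25, so 82 against the stated 80. The point made here does not depend on any of these figures.

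**Direction of skew** (assumed 0-10 scores; skewness by simulation)

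| Assumed shape | Raw | log(x), positive scores only | log(x+1) | log(x+0.1) |
|---|---|---|---|---|
| Clustered high | -0.83 | -1.68 | -1.49 | -1.65 |
| Clustered low, no zeros | +0.69 | -1.43 | -0.22 | -0.87 |
| Floor with 16% zeros | +0.51 | -1.37 | -0.46 | -1.07 |

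Plain log doubles the skew in the first row and overshoots in the other two. Only log(x+1) on the low-clustered score clearly improves symmetry.

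**Mean difference and ratio can disagree.** Let arm A score 1, 1, 9, 9 and arm B score 4, 4, 4.5, 4.5.

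- Arithmetic means: 20/4 = 5.00 and 17/4 = 4.25, so A is higher.
- Geometric means: 81^(1/4) = 3.00 and 324^(1/4) = 4.24, so B is higher.

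**How often the scale would switch.** The article gives no criterion, so one is assumed: Shapiro-Wilk p < 0.05.

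- For the three shapes above, it fired in at least 99.7% of simulated trials.
- For the milder score used below, applied to pooled follow-up scores, it fired in 93% of trials with a treatment effect and 35% without one. The effect itself can thus help to choose the scale.
- With |skewness| > 1 as the trigger, the milder score was never transformed.

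**Power.** From the article: 65 per arm, effect 0.53, two-sided 0.05. Assumed: latent control mean 4, SD 2.3, clipped to 0-10, baseline correlation 0.5.

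- Zeros in usual care: Φ(-4/2.3) = Φ(-1.74) = 4%.
- Exercise-arm mean: 4 - 0.53 × 2.3 = 2.78. Zeros: Φ(-2.78/2.3) = Φ(-1.21) = 11%.
- Analytic check before clipping: 0.53/√(2 × 0.75/65) = 3.49, and Φ(3.49 - 1.96) = 0.94.

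| Analysis | Simulated power (range over repeat simulations) |
|---|---|
| Raw score | 0.92-0.93 |
| log(x+1) | 0.90-0.91 |
| log(x+0.1) | 0.82-0.83 |
| log(x+0.01) | 0.72-0.74 |
| log(x), zeros dropped | 0.69-0.71 |

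With 2,000 trials the Monte Carlo standard error is about √(0.7 × 0.3/2000) = 0.01 at the lower end.

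Sensitivity to the assumptions:

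- At control mean 5 (1.5% and 5% zeros), power is 0.93 raw, 0.79 with zeros dropped and 0.72 with log(x+0.01).
- On a scale starting at 1, it is 0.91 raw and 0.90 logged.
- For the low-clustered score without zeros, log(x+1) gains a little: 0.929 against 0.908.

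**Type I error** (three shapes, 2,000 trials each, standard error √(0.05 × 0.95/2000) = 0.005). Raw ANCOVA gave 0.046 to 0.054, so the transformation is not needed to protect the test. The rule with log(x+1) gave 0.052 to 0.055. Only picking the smallest p-value among raw, log(x+1) and log(x+0.1) raised it, to between 0.061 and 0.082.

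**The case against.** The strongest reply is that the harm depends on facts the article does not give. It states no score ranges, no scoring direction and no expected share of zeros, so neither a floor at zero nor clustering at the high end can be read from it. The transformation is also conditional: if fatigue scores are judged normal, the raw scale stays. A condensed article may leave the normality criterion and any offset to the analysis plan. With an ordinary offset of 1 the loss is about 1 to 3 points of power. For inflammatory markers the sentence describes standard practice. All of this stands, and it limits the size of the point.

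It does not remove the point. The article does more than omit a detail: it commits to one rule for every outcome in the main analysis. The choice of scale by the data and the disregard of skew direction follow from that wording, whatever the score range.

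Three stronger readings are tempting but unsupported.

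- A reader might infer that women with no fatigue would be excluded, biasing the comparison towards no effect. The article describes an intention-to-treat approach with missing values replaced, and nothing in it provides for excluding observed scores. The figure of about 0.70 is therefore a what-if.
- A reader might infer that the switch contradicts a sample size planned on a mean difference. The article gives only an effect size of 0.53, without an SD or a scale.
- A reader might infer that logs belong only to laboratory markers. Other positive measures in the trial, such as strength or pressure pain thresholds, may also suit a log.

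**Conclusion.** The rule is badly fixed for the primary fatigue score and the other questionnaire scores. It looks at the raw variable instead of the residuals, takes no account of the direction of skew, and leaves the primary effect measure to the observed data. These three points need no assumption about score range.

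The problem of zeros is conditional on scores of zero being possible. Under the assumed 0-10 score the cost runs from 1 to 3 points of power with log(x+1), through about 10 points with log(x+0.1), to just over 20 points if zeros were dropped. On a scale starting at 1 it is 1 to 2 points. Type I error stays near 0.05 unless the transformation is picked after seeing results. Severity is minor to moderate: what is mainly lost is a primary effect that is fixed in advance and can be interpreted.

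**What to change.** Replace the transformation sentence with wording such as:

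> *Piper fatigue, QLQ-C30 and MSAS scores are analysed untransformed by baseline-adjusted ANCOVA whatever their distribution. Assumptions are checked on the residuals, and a robust, bootstrap or rank-based analysis is prespecified as a sensitivity analysis. A log is used only for strictly positive, right-skewed measures (for example inflammatory markers), named before the outcome data are seen.*

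Which of the three sensitivity methods to use is a matter of preference; what counts is naming one in advance. The cost is a change of wording and one additional sensitivity analysis. Sample size, data collection and trial conduct do not change.

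### One unadjusted p ≤ 0.05 rule covers about 10 secondary domains (about 15 measures) set beside fatigue in the primary aim, so a chance 'significant' secondary is quite likely

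*Protocol article*

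**What the plan says.** The protocol article names one primary outcome: "The primary outcome is fatigue" (Testing). The power calculation rests on fatigue alone.

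The primary aim is wider. In the Background it compares two exercise regimens and usual care on fatigue and on "the secondary outcomes cardiovascular fitness, muscle strength, function and structure, systemic inflammation, gene activity, health related quality of life, pain, disease and treatment related symptoms". The Abstract words the aim in much the same way.

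The Secondary outcomes section turns these domains into measurements from dynamometry, a cycle test, pressure algometry, muscle biopsy and two questionnaires. Blood is also taken for "genotyping, and for analysis of white cell distribution and epigenetic patterns", among other uses.

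The Statistical analyses section names baseline-adjusted ANCOVA as the main analysis and adds paired tests within groups. It then gives a single threshold: "All tests will be 2-tailed and statistical significance set at" p ≤ 0.05. It does not say whether each ANCOVA yields one three-arm test or separate tests of the arm pairs.

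The list of secondary outcomes is not the same throughout. The Testing section has "Secondary outcomes are return to work, muscle strength and function, cardiovascular fitness, systemic inflammation, mitochondrial density, muscle fibre area, QoL, pain", followed by disease status and treatment-related symptoms. That list includes return to work, which the Abstract and Background put under the second aim. It omits gene activity, which the primary aim includes and which returns as gene expression under the Secondary outcomes heading.

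**The concern.** A rule for all tests is a positive statement about how every secondary result will be judged. Read as written, a secondary outcome that reaches p ≤ 0.05 is called statistically significant by the same standard as fatigue, and it sits under the same aim. With this many outcomes and three arms, some such results are expected by chance. A reader of the trial report could not tell from the protocol which secondary findings are confirmatory and which are leads for further work.

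The point is sharpest for inflammation markers, gene expression and epigenetic patterns. Each is a set of several variables, so one line in the outcome list stands for several tests. This point concerns the secondary outcomes only, not the primary fatigue analysis.

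**Working it through.** **Inputs from the protocol article**
- Threshold: two-sided 0.05 per test (Statistical analyses).
- Arms: three, allocated 1:1:1 (Randomisation process), hence three possible arm pairs.
- Domains in the primary aim (Background): cardiovascular fitness; muscle strength; muscle function; muscle structure; systemic inflammation; gene activity; quality of life; pain; disease and treatment symptoms. That is 9, or 10 if disease and treatment symptoms are counted separately.
- Measures (Secondary outcomes): hand grip, mid-thigh pull, predicted VO2max and pressure pain threshold (4); contractile function, systemic inflammation, fibre area, mitochondrial density and gene expression (5); the five QLQ-C30 function areas named (5); MSAS (1). Total 4 + 5 + 5 + 1 = 15, with each marker set counted once.

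**Inputs assumed**
- No true effect on any outcome.
- A common correlation between outcomes. The article gives none, so 0 to 0.8 is shown.

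The article gives no family-wise error rate to reproduce. Its only stated figure is 5% per test.

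**Step 1. One independent test per outcome.** The chance of at least one false positive is 1 − 0.95^k.
- k = 10: 1 − 0.599 = 40.1%
- k = 13: 48.7%
- k = 14: 51.2%
- k = 15: 1 − 0.463 = 53.7%

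On this basis 50% is passed only from 14 outcomes.

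**Step 2. Correlated outcomes, with and without pairwise testing.** Arm means for k outcomes were simulated under the null in three equal arms (normal, equal correlation, 400,000 replicates). The three-arm test compares the squared deviations of the arm means with the 5% point of chi-square on 2 degrees of freedom. The pairwise version compares each standardised arm difference with 1.96. As a check, a single outcome gives 5% for the three-arm test.

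| Chance of at least one false positive | corr. 0 | 0.3 | 0.5 | 0.8 |
|---|---|---|---|---|
| 10 outcomes, one three-arm test each | 40% | 36% | 29% | 18% |
| 15 outcomes, one three-arm test each | 54% | 46% | 37% | 21% |
| 10 outcomes, three unadjusted pairs each | 73% | 66% | 56% | 37% |
| 15 outcomes, three unadjusted pairs each | 86% | 78% | 66% | 42% |

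**Step 3. Expected number of false positives** (does not depend on correlation).
- One test each: 10 × 0.05 = 0.5; 15 × 0.05 = 0.75.
- Three pairs each: 10 × 3 × 0.05 = 1.5; 15 × 3 × 0.05 = 2.25.

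**Step 4. What is left out.** The table covers between-arm tests at 16 weeks only. The visits at 1, 2 and 5 years repeat those tests. The within-group tests add 15 × 3 = 45 p-values at 16 weeks. Both add to the chance of a false positive. Each outcome with a true effect removes a true null and lowers it.

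**The case against.** The strongest objection is that ordering secondary outcomes and handling their multiplicity is commonly left to a SAP or full protocol. Neither is shown, and a journal article condenses. That stands as far as silence goes: the absence of a hierarchy is not, in itself, a finding. It does not reach the threshold sentence, which the article does state and which covers all tests. A SAP that reserved significance claims for fatigue would have to depart from it.

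Several stronger readings are tempting, and the documents do not support them.

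- *At least 15 outcomes lie in the aim, and a false claim is more likely than not.* The aim names 9 or 10 domains; 15 is a count of measures. A probability above 50% needs every null true and either at least 14 nearly independent outcomes or unadjusted pairwise tests. The article does not say that pairs will be tested, although comparing two regimens with each other and with usual care is hard to do without it. The Background also reports earlier trials with better physical function and quality of life, so some nulls are probably false.
- *There is no hierarchy.* One primary outcome is designated and only that one is powered. What is missing is any distinction in how the secondary results are judged.
- *A significant secondary would satisfy the primary aim even if fatigue showed nothing.* The article does not say so. Its wording only leaves that reading open.
- *A large share of significant biopsy results would be false.* This needs to know how many effects are real. The subset has 45 women. If there were 15 per arm, power at the plan's effect size of 0.53 would be about 29% with an unadjusted t-test. The false share is then 0.05/(0.05 + 0.29) = 15% if half the effects are real, and 0.04/(0.04 + 0.058) = 41% if one in five is. The 0.53 was set for fatigue, and the planned baseline adjustment could raise power.
- *Hundreds of markers will be tested.* No panel size is given. Genotype is not something the intervention changes, so an arm comparison on it is not implied.
- *The outcome lists contradict each other.* Mostly they differ in wording. Return to work can be a secondary outcome that serves the second aim, and gene expression does appear under the Secondary outcomes heading. Equating disease status with recurrence and survival would be a guess.

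**Conclusion.** The point holds in a bounded form. A stated, unadjusted 5% rule covers about 10 secondary domains, or about 15 measures, that share the primary aim with fatigue. With all nulls true and one three-arm test per outcome at 16 weeks, the family-wise error is about 40–54% if outcomes are independent and 29–37% at correlation 0.5. With three unadjusted pairs per outcome at correlation 0.5 it is 56–66%. Even the lowest case in the table, 18%, is more than three times 5%.

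The size depends on the number of outcomes tested, their correlation, how many have true effects and whether pairs are tested. The article settles none of these. The primary fatigue analysis is not affected. The differences between the outcome lists are a minor matter of consistency. The change is worth making because it is cheap and removes an avoidable ambiguity about what secondary results will mean.

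**What to change.** - In Statistical analyses, limit the p ≤ 0.05 significance claim to the primary fatigue analysis. State that secondary outcomes are supportive and will be reported as arm differences with 95% confidence intervals.
- For the multi-marker inflammation, gene-expression and epigenetic analyses, replace the per-test 5% threshold with false-discovery-rate control at a stated level within each panel.
- Use one list of secondary outcomes in the Abstract, the Background aims, Testing and Secondary outcomes. Settle in particular whether gene activity and return to work belong to it.

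If the investigators want confirmatory secondary claims, a short fixed sequence tested after fatigue is an option. It is a trade-off for them to weigh and is not needed to correct the point.

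The cost is wording in the protocol and analysis plan, with no extra participants, visits or assays. The downside is that fewer secondary results can be called statistically significant.
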